#### Control Arm: Target SBP 130–185 mmHg

Participants allocated to this arm will achieve an SBP target of 130–185 mmHg during the following 24–h, following the same protocol, as described in the preceding text.

### Outcomes

#### Primary Outcome

The primary outcome is the rate of subjects with ICH on CT at 24–36 h.

#### Secondary Outcomes

The secondary clinical efficacy outcomes are the disability assessed by overall mRS distribution at 90 days (shift analysis combining scores of 5 and 6), the 3-month favorable functional outcome at 90 days as defined by a mRS 0–2, the 90-day excellent function outcome as defined by a mRS 0–1, the stroke volume as measured by CT at 24–36 h after EVT; stroke volume at 24–36 h, and the change in NIHSS at 24 h.

Safety outcomes are symptomatic ICH defined by an increase of more than 4 points on the NIHSS, parenchymal hematoma type 2, and all-cause mortality at 90 days.

Feasibility outcome is the rate of patients with mean SBP level during BP management <130 mmHg in the experimental group.

### Independent Data Safety Monitoring Board

The purpose of the Independent Data Safety Monitoring Board (DSMB) is to review the unmasked accumulated safety data. The DSMB is composed of two stroke neurologists, one interventional neuroradiologist, and one methodologist, who are not participating in the study and are not affiliated with the sponsor. The role of the DSMB is to review the occurrence of AEs, and it will ensure the balance of complication rates between arms throughout the study by making recommendations to the sponsor.

### Data Collection

The entire study is conducted using electronic case report forms (eCRFs), where all clinical data on enrolled subjects are data entered (single-keyed) by the site personnel. The eCRF was developed using Cleanfile software. The essential data necessary for monitoring the primary and secondary endpoints are identified and managed at regular intervals throughout the trial. Data are monitored by the data management team of the data-management department of University Hospital of Lille by using the predefined rules, and queries will be automatically edited. Finally, an overall automated monitoring is done by the data manager at the end of the data entry. In case of discrepancies, queries will be edited to resolve the problems encountered.

### Sample Size Estimates

Based on the literature (19) and the data from the Endovascular Treatment in Ischemic Stroke (ETIS) registry, we expect an ICH rate of 40% in reperfused subjects with a conventional BP control during 24 h following reperfusion (SBP between 130 and 185 mmHg). We assume that a tight BP control during 24 h following reperfusion (SBP between 100 and 129 mmHg) will be associated with an absolute decrease of 15% (corresponding to a hemorrhage rate of 25%). To detect this effect size, with a two-sided test at the 0.05 level of significance and a power of 80%, 152 subjects per arm will be required. To account for an anticipated rate of 5% of uninterpretable follow-up CT scan, we planned to include a total of 320 subjects (160 per arm).

### Statistical Analyses

Statistical analyses will be independently performed by the Biostatistics Department of Lille University. Data will be analyzed using SAS software (SAS Institute Inc., Cary, NC, USA), and all statistical tests will be performed with a 2-tailed alpha risk of 0.05. Baseline characteristics will be described for each treatment group; categorical variables will be expressed as frequencies and percentages and quantitative variables will be expressed as means ± standard deviation or medians (interquartile range) for non-Gaussian distribution. Normality of distributions will be assessed graphically and by using the Shapiro–Wilk test. No formal statistical comparisons of baseline characteristics will be done; clinical importance of any imbalance will be noted. All analyses will be performed using all randomized participants based on their original group of randomization, according to the intention-to-treat principle. A per-protocol analysis will be considered only for the primary endpoint as a secondary analysis. Per-protocol population will include all randomized patients excluding those with major protocol violations (i.e., patients without reperfusion after EVT, patients with SBP <130 mm Hg at inclusion, patients not achieving their assigned SBP target). The final report will be written, based on the CONSORT statement recommendations.

#### Primary Outcome

The ICH rate on CT at 24–36 h will be reported in each arm, and the primary efficacy analysis will be conducted using a mixed logistic regression model including the center as a random effect and the randomization stratification factor (intravenous alteplase) as a fixed effect. The adjusted odds ratio (OR) will be derived from this model as the treatment effect size (experimental relative to control strategy). We will also calculate adjusted absolute and relative risk differences as effect sizes from the marginal probabilities of ICH rate, estimated by the previous mixed logistic regression model using the method described (20). Since we did not expect missing data on the primary endpoint, no imputation procedure will be applied for primary efficacy analysis. In case of missing data (whatever the reason), a sensitivity analysis will be conducted after handling missing primary endpoint values by a multiple imputation procedure. The imputation procedure will be performed using the main baseline characteristics and treatment group. Missing values will be imputed under a missing at random assumption by using the regression switching approach (chained equation with *m* = 10 imputations) with the predictive mean matching method for quantitative variables and logistic regression models (binary, ordinal, or polynomial) for categorical variables (21). Treatment effect estimates obtained in multiple imputed datasets are combined using Rubin's rules (22).

As exploratory analyses, heterogeneity in treatment effect size on primary outcome across key subgroups will be evaluated by including the corresponding multiplicative interaction terms in the multivariate mixed logistic regression models. From these models, treatment effect sizes (adjusted OR) will be estimated in each subgroup. The following key subgroups are investigated:

- Prior use of intravenous alteplase (yes vs. no)- Age (≤ 80 years vs. >80 years)- Baseline site of occlusion on vascular imaging [isolated middle cerebral artery (MCA) vs. tandem MCA/internal carotid artery (ICA)].

#### Secondary Outcomes

Secondary binary outcomes (symptomatic ICH, parenchyma hematoma type 2, favorable outcome, 90-day all-cause mortality) will be also analyzed similarly to the primary efficacy analysis.

The secondary ordinal outcome [distribution of 90-day after combining scores of 5 and 6 (23)] will be described by the median (interquartile range) for each treatment group and compared using a mixed ordinal logistic regression model including the same fixed and random effects that is used for primary efficacy model. The adjusted common OR per 1-point improvement will be calculated as the treatment effect size.

The change in NIHSS score at 24 h and infarct volume will be calculated and compared between the two treatment groups using the constrained longitudinal data analysis (cLDA) model proposed by Liang and Zeger (19, 20, 24) including the same fixed and random effects as in the primary efficacy model. This model will be used in view of the potential advantages of the cLDA compared to the conventional longitudinal analysis of covariance (ANCOVA) model. In the cLDA, both the baseline and post-baseline values will be modeled as dependent variables using a linear mixed model (using an unstructured covariance pattern model), and the true baseline means will be constrained to be the same for the two treatment groups. The between-group mean differences in 24-h change in NIHSS and infarct volume will be estimated by the time-by-arm interaction as treatment effect size. If the assumption of normality of model residuals is not satisfied (even after log-transformation), nonparametric analysis will be used; absolute changes between baseline and 24 h will be calculated and compared between the two treatment groups using nonparametric analysis of covariance adjusted for baseline values (25).

The other secondary quantitative outcome (stroke volume at follow-up CT scan) will be analyzed using a mixed linear regression model including the same fixed and random effects as the primary efficacy model; the between-group mean differences in stroke volume will be derived from the model as effect size. In case normality of model residuals is not satisfied (even after a logarithmic transformation), nonparametric analysis will be used; stroke volume will be compared using the Mann–Whitney *U* test.

Adverse-related serious adverse events (overall and individual events rates based on subject counts and not on event counts) will be evaluated descriptively in each treatment group, as well as the rate of patients with mean BP levels during BP management <80 mmHg without formal statistical comparison.

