### Randomization

During the first hour following reperfusion, participants will be randomly allocated in a one-to-one ratio to a “tight” BP control, defined as a target SBP between 100 and 129 mmHg (experimental arm), or a standard BP control, defined as target SBP level between 130 and 185 mmHg (control arm), during the following 24 h (Figure 1). The randomization sequence will be provided by an independent statistician (who did not take part in assessing the participants at any point in the study) using computer-generated random numbers with block sizes of four and stratification by center and IV alteplase therapy use prior to EVT. The block size information is not specified in the protocol to ensure that vascular neurologists and interventional neuroradiologists will be not able to anticipate treatment arm assignment. The randomization sequence is implemented in the eCRF system to ensure a centralized real-time randomization procedure. Participants are enrolled and randomized by vascular neurologists or interventional neuroradiologists.

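### The Mann-Whitney fallback for follow-up stroke volume drops the randomization strata and names no effect estimate; the power cost is small

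*Protocol article*

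**What the plan says.** **Randomization.** Allocation is 1:1 in blocks of four, with "stratification by center and IV alteplase therapy use prior to EVT" (Randomization). With four centers (Design), that makes eight strata.

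**Main analysis.** Under Statistical Analyses, Secondary Outcomes, follow-up stroke volume "will be analyzed using a mixed linear regression model including the same fixed and random effects as the primary efficacy model", that is, center as a random effect and alteplase as a fixed effect. The effect size is named: "the between-group mean differences in stroke volume will be derived from the model as effect size".

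**Fallback.** "In case normality of model residuals is not satisfied (even after a logarithmic transformation), nonparametric analysis will be used". The method is then given: "stroke volume will be compared using the Mann–Whitney" U test. No stratum, covariate or effect estimate is attached to this branch.

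**A second assignment of volume.** The preceding paragraph of the same section puts infarct volume, together with NIHSS, under the model abbreviated as cLDA, which treats baseline and later values jointly. Its fallback is "nonparametric analysis of covariance adjusted for baseline values", applied to changes from baseline. The Abstract and the Outcomes section describe only a volume at 24 to 36 h; the Outcomes section lists it twice.

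**The concern.** A data-driven switch from the linear model to the Mann-Whitney test changes two things besides the distributional assumption.

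- **Adjustment.** Center and alteplase disappear. Blocked randomization within strata balances them across arms, so differences between strata cannot bias the comparison. The unstratified test still counts those differences as noise. If the strata predict volume, its standard error is too large and its p-value too high.
- **Reporting.** The main branch has a named effect size and the fallback has none. If the fallback is used, this secondary outcome has a planned test but no planned estimate or interval.

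The second assignment of volume adds to this. A reader cannot tell whether non-normal volume data go to a Mann-Whitney test or to a baseline-adjusted nonparametric ANCOVA. The first needs only a follow-up value; the second needs a baseline volume as well.

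**Working it through.** **1. The article's own figure.** It gives no SD, effect size or power for volume, only a sample size for hemorrhage (40% vs 25%, two-sided 5%, 80% power). With pooled variance and no continuity correction:

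n = [1.96 × √(2 × 0.325 × 0.675) + 0.842 × √(0.40 × 0.60 + 0.25 × 0.75)]² / 0.15² = (1.298 + 0.550)² / 0.0225 ≈ 152 per arm.

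152 / 0.95 = 160 per arm, 320 in total. This reproduces exactly. It bears on volume only by supplying N = 2 × 152 = 304 readable scans.

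**2. Expected size by approximation.** Let R² be the share of variance (on the scale where the shift acts) explained by center and alteplase. With allocation balanced within strata, the Mann-Whitney statistic varies with about √(1 − R²) of the SD the test assumes, so its effective critical value is 1.96 / √(1 − R²). For an assumed shift of 0.32 within-stratum SD, the expected z of a strata-adjusted rank test is 0.32 × √304 / 2 × √(3/π) = 2.79 × 0.977 = 2.73, giving power Φ(2.73 − 1.96) = 77.8%.

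| R² | Effective critical value | Actual type I error | Mann-Whitney power | Loss (points) |
|---|---|---|---|---|
| 0% | 1.96 | 5.0% | 77.8% | 0 |
| 5% | 2.01 | 4.4% | 76.3% | 1.5 |
| 10% | 2.07 | 3.9% | 74.5% | 3.3 |
| 20% | 2.19 | 2.8% | 70.4% | 7.4 |

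**3. Simulation.** Both runs use N = 304, eight strata and blocks of four. Run A: 1,500 trials per scenario, log-normal volume, alteplase in 50%, shift 0.322 of the total SD of log volume; Monte Carlo error of power about √(0.8 × 0.2 / 1500) = 1 point. Run B: shift 0.32 SD; its falling Mann-Whitney power is the pattern expected when the shift is fixed in within-stratum SD. Shift, R², log-SD and alteplase share are assumptions, not figures from the article.

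| R² | A: Mann-Whitney / van Elteren / rank ANCOVA on strata | A: Mann-Whitney type I error | B: Mann-Whitney / rank ANCOVA on strata |
|---|---|---|---|
| 0% | 77.6 / 76.9 / 77.7 | 5.7% | 77.5 / 77.1 |
| 2% | 79.9 / 79.7 / 80.2 | 3.8% | not run |
| 5% | 76.9 / 77.3 / 78.6 | 4.3% | 77.3 / 79.3 |
| 10% | 80.3 / 82.1 / 82.7 | 3.0% | 73.3 / 76.9 |
| 20% | 79.7 / 84.5 / 84.5 | 2.5% | 70.2 / 76.8 |

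The loss against rank ANCOVA is 0.1, 0.3, 1.7, 2.4 and 4.8 points in A, and −0.4, 2.0, 3.6 and 6.6 points in B. Approximation and simulation agree to within about a point in B.

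**4. Is skewness the cause?** No. In run A, on the same skewed data, a strata-adjusted linear model on the raw scale has 52% to 58% power, against 77% to 80% for Mann-Whitney. A rank test copes well with skewness; the loss comes from the omitted strata.

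**The case against.** The case for leaving the plan alone is reasonable, and much of it stands.

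- **The test is valid.** Ignoring the strata makes it conservative. A reader might infer an inflated false-positive rate; the calculation shows the opposite.
- **The gain is small and assumed.** The article gives no center effect, alteplase effect or volume SD. Up to 5% of variance explained, the gain is about the size of simulation error. This stands, and it sets the severity.
- **The fallback may never be used.** A reader might infer that a skewed volume outcome will probably need it. The article requires a log transformation first and gives no distribution and no share of near-zero values, so it does not support that.
- **A much larger gain is tempting to quote.** Adding baseline NIHSS (assumed correlation 0.3 to 0.5) takes rank ANCOVA to 82% to 87% power. That covariate is in no branch of the follow-up stroke-volume plan, so the gain cannot be charged to the Mann-Whitney fallback.
- **The other fallback sets no standard for strata.** The nonparametric ANCOVA is for changes from baseline and names only baseline values. A single follow-up measurement can justify a different method. The contrast therefore does not by itself show that Mann-Whitney is wrong.
- **Silence on an estimate is not exclusion.** A condensed article may leave the estimator to the full protocol or SAP. This weakens the second half of the point: the article names an effect size for one branch and not the other, but does not say that only a p-value will be reported.

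The stated choice itself survives: a specific unstratified test replaces a model that carried both stratification factors.

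**Conclusion.** The point holds as a minor refinement. The fallback for follow-up stroke volume drops center and alteplase, which define the randomization strata and are in the main model, and it names no replacement for the mean difference.

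For N = 304 and an assumed shift of about 0.32 SD, the cost is about 0 to 2 points of power if the strata explain up to 5% of the variance, about 2 to 4 points at 10% and about 5 to 7 points at 20%, with type I error falling to about 3%. If the strata are unrelated to volume, nothing is lost. The article does not say which case applies.

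The outcome is secondary and the branch contingent, so neither the primary conclusion nor the sample size is affected. The double assignment of volume to two models with two fallbacks is a separate textual conflict and arguably the larger defect. Changing the Mann-Whitney sentence alone would leave it in place.

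**What to change.** 1. Replace the Mann-Whitney sentence with a rank analysis adjusted for center and alteplase: rank ANCOVA on the strata, or a van Elteren test. Report a Hodges-Lehmann difference in volume with its 95% CI.
2. Reconcile the two volume paragraphs so that volume has one model and one fallback, matching the outcome as defined (a single volume at 24 to 36 h). If the baseline-adjusted route is kept instead, add center and alteplase to its nonparametric ANCOVA as well, and state the baseline volume that it uses.
3. Adjustment for baseline NIHSS is optional and a separate decision.

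The cost is a sentence or two. The strata are already recorded for randomization. If they are unrelated to volume, van Elteren gives up at most about 1 to 2 points of power (0.7 in run A) and rank ANCOVA essentially none. The change should be made before unblinded data are seen.

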## Discussion

The BP TARGET Trial will be the first randomized controlled trial, with PROBE design, designed to compare the effect of two SBP target strategies, after EVT reperfusion, on ICH. We hypothesized that an SBP target of 100–129 mm Hg will be associated with a decreased risk of ICH. ICH on CT at 24 h was chosen as the primary outcome, considering the evidence supporting that elevated SBP is associated with ICH (10), a consequence of reperfusion injury, and associated with a worse prognosis. Additionally, recent evidence has shown that patients with mean SBP between 101 and 120 mmHg have lower odds of symptomatic ICH, when compared to those with SBP > 140 mmHg (13). Obviously, achieving BP control strategies in subjects with persistent arterial occlusion may not have the same consequence as that in subjects with complete reperfusion. In this context, we choose to study a homogeneous population with documented reperfusion of the anterior circulation.

Retrospective data from AIS subjects treated with EVT reveal a different impact of SBP values based on the reperfusion status (10). In fact, in subjects with successful reperfusion, maximum SBP correlates with worse functional outcome and ICH occurrence (10). Still, the observed relationship between BP and prognosis may be due to the fact that patients with a larger volume of brain ischemia have greater elevations in BP (26). Thus, BP elevation may be a marker of poor outcome, rather than the cause. Although analyses will include stratification on age, tandem lesions, or in participants receiving IVT, these are only exploratory and not designed to have the power to address the effect of the 100–130 mm Hg SBP target. In addition, we cannot exclude a differential effect due to the drug (e.g., reduced BP variability with calcium channel blockers compared to beta blockers).

## Summary and Conclusions

No previous head-to-head randomized trials have directly compared the efficacy of different SBP targets after EVT reperfusion. This prospective trial aims to determine whether a target SBP < 130 mm Hg after EVT reperfusion can reduce the risk of ICH.

## Ethics Statement

The studies involving human participants were reviewed and approved by Comité de Protection des Personnes Sud Méditerranée IV. The patients/participants provided their written informed consent to participate in this study.
